### Study setting and timeline

2.2

The trial takes place in six mental health services from inner and outer London, a large university town in the southeast of England and the surrounding suburban and rural communities, and a large costal conurbation in the south-west of England and its surrounding rural communities. The populations served vary considerably in the degree of social deprivation, available community resources and the structure of local mental health services. To commence recruitment, services must meet adequate fidelity to the model of care (see ‘monitoring intervention delivery’).

Participant recruitment commenced in the first site in June 2019, and all other sites were able to open to recruitment by January 2020. The protocol was registered during this set-up period (in December 2019). Recruitment was suspended in March 2020 (to reduce pressure on health services in the initial months of the COVID-19 pandemic) and restarted across the six sites from August 2020 to December 2020. Recruitment will stop in December 2021, the primary outcome will be available from December 2023, and data analysis will commence in early 2024.

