### Trial clusters and randomisation

2.3

Trial clusters are defined in relation to groups of general practices (clinics where family physicians see patients). Inclusion criteria are as follows:•Each cluster must consist of two to four geographically co-terminous general practices (their catchment areas share a geographical boundary). There must be a clear and pre-existing shared referral pathway to a community mental health service, and a total of 65–75 patients per year referred to mental health crisis services.•Each general practice within the cluster should refer only within the catchment area of the community mental health service, refer at least 10 people per year to mental health crisis services, and have 2000 or more patients registered with the practice.

Once a mental health service has been recruited, GP practices within its catchment area are assessed and grouped into clusters in line with the cluster eligibility criteria. Relevant details of all the clusters from each catchment area are then sent to the trial statistician who randomly allocates in a 1:1 ratio to Open Dialogue or TAU. Cluster randomisation is stratified by catchment area of the local mental health services and restricted randomisation [11] is used to balance two continuous aggregated cluster-level covariates ‘average GP list size’ and ‘average IMD deprivation rate 2015’ [46] across the two trial arms and the strata. Where there are changes to general practices that form the basis of clusters (for example, two initially separate general practices merging to form a single practice) after cluster allocation, we aim to preserve selection of participants from the original clusters as far as possible.

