#### Sample size

2.5.1

Thirty clusters, with 19 participants each, provide an initial sample size of 570 participants, with a projected 540 participants being observed during the follow-up period. Following Freedman's [19] formula, a total of 157 participants was calculated as being needed to relapse during the 24-month follow-up period to detect an HR = 0.589 or more, with 90% power using a log-rank test at the 5% significance level. Following a method by Rutterford, Copas, and Eldridge [51], this number was inflated by our design effect (design effect = 1 + (obs. Per team cluster - 1) ICC = 1 + 17 × 0.04 = 1.68; based on a typical intra-cluster correlation in cluster randomised trials of ICC = 0.04; [18] to calculate the total number of relapses needed to adjust for clustering. This gives a requirement of 264 relapses during the 24-month follow-up period. Assuming an average relapse rate of 49%, this requires an effective sample size of 264/0.49 = 538 participants.

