### Statistical analysis

2.6

The primary outcome, time to relapse from recovery, will be analysed using Cox regression, where time to relapse will be the dependent variable, with fixed explanatory variables of trial arm, and stratification factor (catchment area of the mental health service), and cluster-level balancing variables of general practice list size, and Index of Multiple Deprivation. The model will also contain a random intercept that varies at the level of the catchment area to account for general practice cluster effects.

This modelling will supply an estimate of the hazard ratio of relapse comparing Open Dialogue with TAU and an associated 95% confidence interval. In the (unlikely) event that covariates are missing or that aspects of the Open Dialogue intervention (e.g. number of contacts between participants and teams) drive censoring times, we will employ multiple imputation for survival outcomes as described in White and Royston [61].

Continuous secondary outcomes measured at several time points will be analysed using linear mixed models. In these models the available post-allocation measures of the secondary outcome variables form the dependent variable, with trial arm, time, trial arm x time interactions terms, stratification, and balancing variables as explanatory variables. To account for the correlation between repeated measures taken on the same subject, subject-varying random effects will be included in the model. To account for remaining correlation between outcomes from patients from the same cluster, a further cluster-varying random intercept will be included in the model.

Distributional assumption will be checked and continuous outcomes arising from skewed distributions suitably transformed before analysis.

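### The primary Cox model's random intercept is written at the catchment area, already a fixed effect, and not at the randomised general-practice cluster

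*Protocol article*

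**What the plan says.** All references are to the protocol article.

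- **Trial clusters and randomisation.** The randomised unit is a group of practices: "Each cluster must consist of two to four geographically co-terminous general practices". Catchment is the stratum: "Cluster randomisation is stratified by catchment area of the local mental health services".
- **Study setting and timeline; Sample size.** The two levels differ in number. On services: "The trial takes place in six mental health services". On clusters: "Thirty clusters, with 19 participants each, provide an initial sample size of 570 participants, with a projected 540 participants being observed".
- **Sample size.** The number of relapses is inflated for correlation within clusters: "design effect = 1 + (obs. Per team cluster - 1) ICC = 1 + 17 × 0.04 = 1.68".
- **Statistical analysis, primary outcome.** The fixed effects are trial arm, "stratification factor (catchment area of the mental health service"), list size and deprivation index. The next sentence reads: "The model will also contain a random intercept that varies at the level of the catchment area to account for general practice cluster effects". No other cluster term, robust variance or cluster-level test is given for this model.
- **Statistical analysis, continuous secondary outcomes.** Besides the subject-level effects, "a further cluster-varying random intercept will be included in the model".

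**The concern.** Arm is allocated to general-practice clusters, so the arm contrast carries the variation between clusters within a catchment. The model has to represent that variation if the standard error is to be right. A catchment-level term cannot do so, because the clusters within a catchment are split between the arms and share one catchment effect. Here it adds nothing at all: the fixed effect already gives each catchment its own level.

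Read literally, the primary model therefore treats participants in the same cluster as independent once catchment, list size and deprivation are allowed for. The hazard ratio would be reported with too narrow a 95% confidence interval and too small a p-value. The trial would have recruited enough participants to pay for clustering and then not have allowed for it in its main analysis. The secondary outcomes would be analysed at the right level and the primary outcome would not.

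**Working it through.** **1. Reproduce the plan's figures.** Inputs from Sample size: HR 0.589, 90% power, 5% significance level (two-sided reproduces the figure), ICC 0.04, relapse rate 49%.

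- Freedman: (1.960 + 1.282)² × (1.589/0.411)² = 157.06. Stated: 157.
- Observed per cluster: 540/30 = 18. Design effect: 1 + 17 × 0.04 = 1.68.
- Relapses: 157 × 1.68 = 263.8. Stated: 264.
- Participants: 264/0.49 = 538.8. Stated: 538.

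The figures reproduce. The 1.68 uses 18 per cluster, which is 540 over 30 general-practice clusters. Over six catchments it would be 540/6 = 90. The sample size therefore places the correlation at the general-practice cluster.

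**2. Why the intercept is redundant.** With a fixed effect for every catchment, nothing is left at that level for a random intercept to explain. Its predicted values are zero whatever its variance, so the data carry no information on that variance.

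**3. Size of the error by formula.** If the variance between clusters is not modelled, the standard error is too small by √DE, and the true two-sided error of a nominal 5% test is 2 × [1 − Φ(1.96/√DE)].

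At DE = 1.68: √1.68 = 1.296; 1.96/1.296 = 1.512; error = 0.1305, about 13%. Equivalently, a nominal 95% interval covers about 87%.

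| At risk per cluster | Residual ICC | DE | Type I error |
|---|---|---|---|
| 12 | 0.02 | 1.22 | 7.6% |
| 12 | 0.04 | 1.44 | 10.2% |
| 12.6 (70% of 18) | 0.02 | 1.232 | 7.7% |
| 12.6 (70% of 18) | 0.04 | 1.464 | 10.5% |
| 18 | 0.02 | 1.34 | 9.0% |
| 18 | 0.03 | 1.51 | 11.1% |
| 18 | 0.04 | 1.68 | about 13% |
| 18 | 0.05 | 1.85 | 15.0% |
| 19 | 0.04 | 1.72 | 13.5% |
| 19 | 0.05 | 1.90 | 15.5% |

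The document gives 18 and 19 per cluster and ICC 0.04. The other values are assumptions to show the range.

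**4. Check by simulation.** There were 2,000 null trials per setting, with 30 clusters in six catchments and 49% relapsing. Cluster frailty was log-normal, set to the listed ICC of relapse by the end of follow-up. The Cox model had arm, catchment and two cluster-level covariates as fixed effects. Assumed, not in the document: clusters split 4, 4, 4, 6, 6, 6 over catchments; covariates unrelated to outcome; no variation between catchments.

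| ICC, per cluster | No random effect | Catchment intercept (as written) | General-practice cluster intercept |
|---|---|---|---|
| 0, 18 | 5.3% | 5.3% | 3.7% |
| 0.02, 18 | 9.7% | 9.7% | 5.5% |
| 0.04, 18 | 14.1% | 14.1% | 5.7% |
| 0.05, 18 | 16.0% | 16.0% | 6.3% |
| 0.04, 12 | 11.5% | 11.5% | 5.1% |

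The Monte Carlo standard error at 14.1% is √(0.1405 × 0.8595/2000) = 0.8 percentage points. The catchment intercept left the rejection rate unchanged in every setting, which confirms step 2. In the first two settings its variance was iterated and stayed at its starting value of 0.1; in the other three it was held at 0.1. With the intercept on the randomised cluster and an ordinary Wald z-test, the error was 5.1–6.3% in the clustered settings.

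**The case against.** **It is a slip, not a decision.** The sentence names general-practice cluster effects as its purpose, the sample size allows for them, and the secondary models put the intercept at the right level. This stands. A reader might infer that the trial has chosen to ignore clustering. The document does not support that, and the inflated error arises only if the sentence is implemented as written.

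**The size depends on assumptions.** A reader might also infer a flat type I error of 13–15%. That is too firm. The ICC of 0.04 is described as typical of cluster randomised trials and is not an estimate for this outcome. Catchment, list size and deprivation absorb whatever part of it they explain. Only participants who have recovered can relapse, so fewer than 18 per cluster may be at risk. Each of these can lower the figure, and the range in the working reflects them.

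**Catchment area might mean the practices' own areas.** Trial clusters and randomisation does use the term for practices as well. But the primary-model text ties it to the mental health service one sentence before, and a single practice would still not be the randomised unit.

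**The SAP may settle it.** It is not shown and may already be right. This is not a detail left to the SAP, however: the article states the level and states it wrongly. If the SAP names the cluster, the two documents need reconciling.

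**Conclusion.** The sentence is wrong as written and must be corrected, because it specifies the primary analysis. The random intercept duplicates a fixed effect and leaves the randomised cluster out of the model, in contradiction to the randomisation, the sample size and the secondary models.

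Implemented literally, the two-sided type I error is about 13–14% instead of 5% at the plan's own values: about 13% by formula and 14.1% by simulation. These figures take all of the 0.04 to lie between clusters within catchments. Over residual ICCs of 0.02–0.05 and 12–19 at risk per cluster the range is roughly 8–16%. The direction is the same in every clustered setting examined; the exact figure is conditional. The document gives no ground for saying that the sponsor intends to disregard clustering, or that the final analysis will.

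**What to change.** Change the sentence to: *The model will also contain a random intercept (shared frailty) that varies at the level of the randomised general-practice cluster (30 levels), with catchment area as a fixed effect only.* Check that the SAP states the same level.

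This needs no new data and no change to the sample size, since the 264 relapses already include the design effect of 1.68. The only downside is a wider confidence interval, which is the correct one. A small-sample reference distribution for the arm effect is an optional refinement and not part of this correction.

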### Outcomes

2.5

The primary outcome is time, in days, to ‘relapse’ following recovery. Recovery is defined as the absence of significant symptoms and presence of adequate social functioning; and relapse as the return of significant symptoms and deterioration of social functioning [7]. A summary of each participant's social circumstances, mental health, and type of response from health care providers for the two-year follow-up period is created primarily from their electronic medical records and research contacts. This summary is reviewed by a panel of trained raters, blind to treatment allocation, who use it to estimate the presence and date of any recovery or relapse using an established method [7]. Any information that might unblind the panel is redacted, and the panel's estimation of allocation is monitored.

For a description of secondary outcomes, measures, potential mediators, and family/carer measures see Table 1 below.

**Table 1 t0005:** Details of secondary outcomes, potential mediators, and family/carer measures.

	Outcome	Measure	Description of measure
Secondary outcomes	Recovery	Time in days to initial recovery, and the total number of days spent in recovery [7]	An expert panel estimate based on 24 monthly summaries of a person's social circumstances, mental health, and type of response from healthcare practitioners. See assessment method described for the primary outcome measure.
	Service-user defined recovery	Questionnaire on the Process of Recovery (QPR) [40]	A 15-item self-report measure developed to assess intrapersonal and interpersonal functioning, measured at 3, 6, 12, and 24 month time points (test-retest reliability *r* = 0.769 [40]).
	Health-related quality of life	EQ-5D-5L [25]	A self-report measure yielding a 5-digit number describing self-rated health state measured, during the first research interview, and at 3, 6, 12, and 24 months post initial crisis presentation **(**intraclass correlation coefficient = 0.75 [30]).
	Service use and societal costs	Client Service Receipt Inventory (CSRI) [8] Plus the number of and length in days of psychiatric admissions, and number of accepted referrals to crisis services in the 24 months after the initial crisis	A tool used to collect information on service utilisation, accommodation, income, and other costs measured at 3, 12, and 24 months post the initial crisis presentation.

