#### Methods for additional analyses

2.6.1

Mediation modelling will be performed to investigate the hypothesis that improvements in times to relapse under Open Dialogue are brought about by enhanced quality/size of the social network or by higher levels of shared decision-making. Specifically, we will estimate the direct (non-mediated by networking) and indirect (mediated by networking) effects of Open Dialogue on time to relapse. For this purpose, social network quality, social network size, and shared decision-making at 6 months will be assessed as potential mediators. Confounders of the relationship between network quality and relapse (e.g. social network score or symptom severity at first research interview) will be measured and included in the mediation modelling. A complier average causal effect (CACE) analysis will also be undertaken to estimate the effect of actually receiving the intervention using instrumental variables regression.

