### Data collection

4.2

Primary data are collected during research interviews and are extracted from electronic medical records (see Table 2 for a full schedule of data collection).

**Table 2 t0010:** Data collection time-points.

Data source	Data collected	True baseline (crisis)	First research interview	3 months	6 months	12 months	24 months
RCT participants	Sociodemographic information		X				
	Brief Psychiatric Rating Scale (BPRS)		X				
	Health related quality of life (EQ-5D-5L)		X	X	X	X	X
	Client Services Receipt Inventory (CSRI)			X		X	X
	Social Provisions Scale (SPS)		X	X	X	X	X
	Lubben Social Network Scale (LSNS-6)		X	X	X	X	X
	Questionnaire about the Process of Recovery (QPR)			X	X	X	X
	Client Satisfaction Questionnaire (CSQ)			X		X	X
	Modified Dyadic OPTION scale			X	X		X
Review of records	• Diagnoses (if any) • Drug/alcohol misuse • Contact with secondary mental health services and crisis referrals • Number of hospital visits • Inpatient stays • Other long-term health problems	X (Extracted for the 6 months prior to baseline)					
	Number of clinical meetings	Ongoing throughout trial participation					
	Relapse and recovery summary	Primary outcome assessed at 24 months					
	Hospitalisation	For the 6 months prior to baseline, and at 12 and 24 months					
	Crisis referral	For the 6 months prior to baseline, and at 12 and 24 months					

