#### Baseline and follow-up research interviews

4.2.1

The baseline timepoint is the date of the crisis referral. This referral takes place after cluster randomisation, but before a potential participant has been assessed as meeting eligibility criteria prior to consent. The first research interview is conducted as close as possible to the date of the crisis referral (baseline) after consent is provided. Research interviews either occur in person (i.e. at the research site or at participant's homes) or over the telephone (the primary method of data collection during the COVID-19 pandemic). Follow-up interviews are undertaken at 3, 6, 12, and 24 months from baseline (see Fig. 1).

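### The mixed models for continuous secondary outcomes include no participant-level pre-crisis covariate, although service use in the 6 months before the crisis is collected; the outcome time points for EQ-5D-5L also need naming

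*Protocol article*

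**What the plan says.** Section 2.6 (Statistical analysis) sets the scope: "Continuous secondary outcomes measured at several time points will be analysed using linear mixed models". The response is then defined by this phrase: "the available post-allocation measures of the secondary outcome variables form the dependent variable". The fixed effects listed are arm, time, the interaction of the two, the stratification factor and the cluster-level balancing variables. Random effects for subject and cluster complete the specification. No participant-level starting value is listed.

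The data schedule (section 4.2, Table 2) shows hospitalisation and crisis referrals collected "For the 6 months prior to baseline, and at 12 and 24 months". The closing text of section 2.5 (Outcomes) confirms that service use in the 6 months before the index crisis is taken from medical records. Table 1 lists the number and length in days of psychiatric admissions, and accepted crisis referrals, as secondary outcomes over 24 months.

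On timing, section 4.2.1 says of the crisis referral, which is the baseline date: "This referral takes place after cluster randomisation". The first research interview follows referral and consent. EQ-5D-5L is measured "during the first research interview, and at 3, 6, 12, and 24 months post initial crisis presentation". QPR, CSQ-8 and CSRI have no first-interview measure.

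**The concern.** Two things stand out in the section 2.6 specification.

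First, the trial extracts a pre-crisis version of its own service-use outcomes, but the stated covariate list makes no use of it. Prior admissions and referrals plausibly predict later ones, so leaving them out gives up precision. They also matter for balance. Clusters are allocated before any participant presents, local staff then make the first approach, and researchers are not blind to allocation. The exclusion of people who have already received Open Dialogue could also act differently in the two arms. Restricted randomisation on list size and deprivation is at cluster level and does not address differences in who is recruited.

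Second, because allocation precedes the referral, every questionnaire measure is post-allocation. Read literally, the first-interview EQ-5D-5L becomes an outcome alongside the follow-up values, whether or not that was meant.

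**Working it through.** **The plan's own figures.** No precision or power figure is given for any secondary outcome. The clustering inputs come from section 2.5.1 and reproduce:
- Design effect: 1 + 17 × 0.04 = 1.68, with 540/30 = 18 observed per cluster.
- Freedman's formula at HR 0.589, two-sided 5%, 90% power: 157.06 relapses (157 stated).
- 157 × 1.68 = 263.8 (264 stated), and 264/0.49 = 538.8 (538 stated).

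**Gain from a pre-crisis covariate.** Inputs: ICC 0.04 and m = 18, borrowed from the relapse calculation and so an assumption for any other outcome; r, the correlation between the pre-crisis and follow-up value, which the documents do not give. The contrast is at one time point.

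- If r holds at participant and cluster level, the variance factor is 1 − r².
- If only within-cluster variance falls, the factor is [(1 − ICC)(1 − r²) + m × ICC] / 1.68 = [0.96(1 − r²) + 0.72] / 1.68.

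| r (assumed) | Factor, both levels | Interval narrower by | Factor, within cluster only | Interval narrower by |
|---|---|---|---|---|
| 0.2 | 0.96 | 2% | 0.98 | 1% |
| 0.4 | 0.84 | 8% | (0.806 + 0.72)/1.68 = 0.91 | 5% |
| 0.5 | 0.75 | 13% | (0.720 + 0.72)/1.68 = 0.86 | 7% |
| 0.6 | 0.64 | 20% | (0.614 + 0.72)/1.68 = 0.79 | 11% |

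The narrowing is 1 minus the square root of the factor. The row for 0.2 is included because a 6-month count may be only weakly related to use over 12 or 24 months. These factors suit a continuous outcome under a linear model, so they illustrate inpatient days. They do not give a figure for admission or referral counts.

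**First-interview EQ-5D-5L on the outcome side.** A generalised least squares calculation used 270 per arm, complete data, equal correlation ρ between all five occasions, no clustering and unit variance. The variance of the 24-month arm contrast was:
- first interview as an outcome, full arm × time interaction: 0.00741;
- first interview ignored: 2/270 = 0.00741;
- first-interview mean constrained equal in the two arms: 0.00741 × (1 − ρ²), that is × 0.91, 0.75 and 0.51 at ρ = 0.3, 0.5 and 0.7.

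So the literal wording costs the later time-specific contrasts nothing compared with ignoring the first interview. Precision is gained only by adjusting or constraining, and that requires treating the value as unaffected by arm.

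**Can it be so treated?** Section 3 has Open Dialogue teams offering care from initial presentation. Section 4.1 allows usually 48 hours, or longer, before consent, and the interview comes after consent. The 6-month records end at the crisis, and people who previously received Open Dialogue are excluded, so for the records there is no such doubt.

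**The case against.** A reader might infer that the plan wrongly omits a baseline EQ-5D-5L and loses precision by placing it among the outcomes. The documents do not support this. Table 2 separates the true baseline, the crisis, from the first interview. The interview may follow the start of allocated care, so adjusting for it could remove early effect and could not distinguish that effect from recruitment imbalance. Section 2.6.1 does use values such as "social network score or symptom severity at first research interview", but as confounders of the mediator–relapse relationship. Such confounders need not precede allocation, so this is no warrant for adjusting the arm comparison. As shown above, the outcome-side placement is not itself the cause of lost precision.

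A reader might also infer that the mixed models wrongly leave out pre-crisis admission and referral counts. Those outcomes are counts, section 2.6 restricts these models to continuous outcomes, and the article states no count model. Section 4.3 refers full analysis details to the SAP, which is not shown, so that silence is no error. Inpatient days are the arguable exception: Table 2 records hospitalisation at 12 and 24 months, although Table 1 can be read as a single 24-month total.

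Nor does the point extend to QPR and CSQ-8, which have no first-interview value and for which no gain can be computed.

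All of this stands. It does not reach the pre-crisis records, which precede the index crisis and are already collected, or the ambiguity about which EQ-5D-5L occasions are outcomes.

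**Conclusion.** The point holds as an improvement to a specification that the article states explicitly. The covariate list has no participant-level pre-crisis term, although suitable values are extracted from records and the timing objection does not apply to them. For inpatient days, and for r between 0.4 and 0.6, intervals would narrow by 8% to 20% if r holds at both levels, or about 5% to 11% if only within-cluster variance falls. A weaker correlation would give less. These figures rest on an assumed r and on an ICC of 0.04 carried over from the relapse calculation. The protection against recruitment imbalance cannot be quantified from the documents.

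For EQ-5D-5L the finding is an ambiguity of wording, to be settled by naming the time points. It is not a demonstrated bias. The primary analysis and the sample size are unaffected.

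**What to change.** 1. Pre-specify the matching value from the 6 months before the crisis as a covariate for each service-use outcome: inpatient days under the stated mixed model, and admissions and accepted crisis referrals in whatever count model is used.
2. Replace the post-allocation wording with named time points; for EQ-5D-5L, 3, 6, 12 and 24 months.
3. Use the first-interview EQ-5D-5L as a covariate in a supportive analysis only, stating that it is measured after allocation and possibly after care has begun.

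The cost is analysis wording, agreed before database lock. No new data are needed. Items 1 and 2 carry no risk of adjusting away a treatment effect; item 3 does, which is why it should not be the main analysis.
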